#### 11.2.3 Statistical Analysis of Efficacy Data

The efficacy endpoints will be analyzed with the FA Set as the primary analysis set and the PP Set as the secondary analysis set, and for different trends in the analysis results between the two sets, the cause should be identified.

- 1) Primary efficacy endpoint  
For the mean percent change from baseline in LDL-C at Week 12, descriptive statistics (mean, standard deviation, median, minimum, and maximum) will be presented, and to demonstrate that LDL-C lowering effect in the study group is superior to that in the control group, the independent samples t-test or the Wilcoxon rank sum test will be performed.
- 2) Secondary efficacy endpoints
  - ① For the mean percent changes from baseline in lipid parameters at Week 12, descriptive statistics (mean, standard deviation, median, minimum, and maximum) will be presented, and the mean percent changes will be compared between the study group and the control group using the independent samples t-test or the Wilcoxon rank sum test.  
\* Lipid parameters: HDL-C, TG, total cholesterol, Apo-A1, Apo-B, non-HDL-C/HDL-C ratio, total cholesterol/HDL-C ratio, LDL-C/HDL-C ratio, Apo-B/Apo-A1 ratio
  - ② For the mean changes from baseline in HbA1c and glucose at Week 12, descriptive statistics (mean, standard deviation, median, minimum, and maximum) will be presented, and the mean changes will be compared between the study group and the control group using the independent samples t-test or the Wilcoxon rank sum test.
  - ③ The percentage of subjects achieving the target LDL-C by risk group at Week 12 after administration will be set as follows and compared between the study group and the control group using the chi-square test or the Fisher's exact test.

- Achievement of LDL-C in high-risk group: Percentage (%) of subjects achieving LDL-C < 100 mg/dl
- Achievement of LDL-C in very high-risk group: Percentage (%) of subjects achieving LDL-C < 70 mg/dl
- ④ The percentage of subjects achieving the target non-HDL-C by risk group at Week 12 after administration will be set as follows and compared between the study group and the control group using the chi-square test or the Fisher's exact test.
  - Achievement of non-LDL-C in high-risk group: Percentage (%) of subjects achieving non-HDL-C < 130 mg/dl
  - Achievement of non-LDL-C in very high-risk group: Percentage (%) of subjects achieving non-HDL-C < 100 mg/dl

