### 6.2 Group Assignment

#### 6.2.1 Randomization

In this study, only the subjects who meet the inclusion criteria will be randomized in a 1:1 ratio. In order to assign subjects to each group in balance, a restricted block randomization method that include study site and risk group result as strata, will be applied, and the block size will be selected among multiples of 2 (e.g., 2, 4, 6, etc.) A randomization table will be created by the biostatistician in charge of randomization using the IWRS, SAS, etc. In order to randomize subjects who meet the inclusion/exclusion criteria and are considered to be eligible to participate in the study based on the risk group information, a stratification variable, randomization will be automatically performed by the IWRS, and the randomization result can be found on the electronic case report form (e-CRF).

When conducting a multi-center study, it is important to standardize the study procedures according to the shared protocol so that the study can be conducted in a similar manner at all sites. Thus, the distribution of subjects should be the same among the study sites to assume that the therapeutic effect would be the same among the study sites.

Once data required to assign an allocation number (AN) are entered on the e-CRF, subjects will be randomized to either the study group or control group by the IWRS. If an AN is erroneously assigned due to errors in the data entry, etc., the already assigned AN cannot be corrected, and the study will proceed as randomized. Subjects enrolled afterwards will be automatically assigned an AN in the order of numbers set in the system.

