## **10.2 Efficacy Endpoints and Assessments**

### **10.2.1 Primary Efficacy Endpoint**

Percent change from baseline in LDL-C at Week 12

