### 11.4 Rationale for Determination of Sample Size

This study aims to demonstrate that the study group (Lipilou 20 mg) is superior in lowering the percent change in LDL-C at Week 12 to the control group (Lipilou 10 mg) in patients with primary hypercholesterolemia, and to that end, the following hypothesis was set.

<Hypothesis>

$$H_0: \mu_t - \mu_c = 0 \text{ vs. } H_1: \mu_t - \mu_c \neq 0$$

$\mu_t$ : Percent change from baseline in LDL-C at Week 12 in the study group

$\mu_c$ : Percent change from baseline in LDL-C at Week 12 in the control group

To test the above hypothesis, the FDA approval data on rosuvastatin was reviewed, which showed that the percent changes in LDL-C at Week 12 after administration were -50% ( $\pm 13$ ) for rosuvastatin 20 mg and -44% ( $\pm 12$ ) for rosuvastatin 10 mg. Thus, the difference between the groups was assumed to be -6%.

| % change, mean±sd | Rosuvastatin 10 mg
(n=44) | Rosuvastatin 20 mg
(n=44) |
|-------------------|------------------------------|------------------------------|
| Baseline          | 229±45                       | 237±48                       |
| Week 12           | -44±12                       | -50±13                       |

Based on the result above, the difference in the percent change between Lipilou 20 mg and Lipilou 10 mg and the standard deviation were assumed and the number of subjects was calculated using the formula below. The difference between the groups and the standard deviation were assumed to be -6 and 13, respectively, and a two-sided significance level of 5% (2.5% for one-sided) with a test power of 90% was applied. The number of subjects calculated was 99 subjects per group, and considering a 20% dropout rate, a total of 248 subjects (124 subjects X 2 groups) need to be enrolled.

$$n = \frac{2 \times (Z_{1-\alpha/2} + Z_{1-\beta})^2 \times \sigma^2}{\epsilon^2} = \frac{2 \times (1.96 + 1.28)^2 \times 13^2}{(-6)^2} = 2 \times \frac{99}{(1 - 0.2)} \cong 248$$

$\epsilon$  = Difference between the groups (-6)  
 $\sigma^2$  = Variance (13)

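### The protocol fixes an unadjusted primary test that leaves out baseline LDL-C and the randomisation strata; one ANCOVA would be more precise at no extra cost

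*Protocol*

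**What the plan says.** The primary endpoint in Protocol 10.2.1 is "Percent change from baseline in LDL-C at Week 12". For the comparison of the two doses, 11.2.3 gives aim and test in one sentence: to show that lowering with the 20 mg tablet "is superior to that in the control group, the independent samples t-test or the Wilcoxon rank sum test will be performed". The synopsis repeats the same pair of tests. The continuous secondary endpoints (other lipids, HbA1c, glucose) get the same pair. Section 11 names no covariate, model or stratified test.

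The design uses more information than the analysis does. Under 6.2.1, "a restricted block randomization method that include study site and risk group result as strata, will be applied", with 1:1 allocation. Lipids are measured at the central laboratory before treatment (10.1), so baseline LDL-C is available for every randomised subject. The entry floor for LDL-C depends on risk group: 100 mg/dl for high risk and 70 mg/dl for very high risk (5.2).

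Section 11.4 states the hypothesis as a difference between two means. Its sizing assumption reads: "The difference between the groups and the standard deviation were assumed to be -6 and 13, respectively". For the error rates, the same section records that "a two-sided significance level of 5% (2.5% for one-sided) with a test power of 90% was applied".

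**The concern.** Two features of the stated test do not fit the design.

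- **Unused information.** Stratified blocks force the arms to be balanced within site and risk group. The unadjusted t-test still counts between-stratum variation as noise, so if the strata predict response its standard error is too large. Baseline LDL-C is not balanced by design. It enters only as the denominator of the percent change, so any remaining dependence on baseline stays in the residual variance, and a chance imbalance goes uncorrected.
- **A second test with a different target.** The hypothesis and the sample size concern a mean difference. The rank sum test neither tests nor estimates that quantity directly, yet it stands as an equal alternative for the trial's one confirmatory claim.

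At stake are precision and a clear primary estimate. The validity of the trial is not in question.

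**Working it through.** **Inputs from 11.4:** difference 6 percentage points, SD 13, two-sided 5%, power 90%, 99 evaluable per group, 20% dropout. **Assumed, because the protocol does not give it:** R², the share of the variance of percent change explained by baseline LDL-C, risk group and site, taken from 0 to 0.20.

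**1. The protocol's own figure.** n = 2 × (1.96 + 1.28)² × 13² / 6² = 2 × 10.4976 × 169 / 36 = 98.56, so 99 per group. Then 99 / 0.8 = 123.75, so 124 per group and 248 in total. It reproduces. Power at 99 per group is 90.1% by the normal approximation and 89.8% by the non-central t.

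**2. Power of an adjusted analysis.** Replace the SD by 13 × √(1 − R²). The non-centrality is 6 / (SD × √(2/99)). The 95% CI half-width is 1.96 × SD × √(2/99).

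| R² (assumed) | Residual SD | Non-centrality | Power, 99 per arm | CI half-width |
|---|---|---|---|---|
| 0 | 13.00 | 3.25 | 89.8% | 3.62 |
| 0.05 | 12.67 | 3.33 | 91.2% | 3.53 |
| 0.10 | 12.33 | 3.42 | 92.6% | 3.44 |
| 0.20 | 11.63 | 3.63 | 95.1% | 3.24 |

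The few degrees of freedom spent on covariates are ignored. The R² = 0 row is the unadjusted analysis.

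**3. Real level of the unadjusted t-test when the strata matter.** With balanced strata, the true variance of the difference is 2σ²(1 − R²)/n, but the t-test estimates 2σ²/n. Its real level is therefore 2 × [1 − Φ(1.96 / √(1 − R²))].

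- R² = 0.05: 1.96 / 0.975 = 2.01, level 4.4%.
- R² = 0.10: 1.96 / 0.949 = 2.07, level 3.9%.
- R² = 0.20: 1.96 / 0.894 = 2.19, level 2.8%.

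A simulation with 20 balanced strata of 10 subjects (20,000 trials) gave 4.4, 4.1 and 2.9%. The stratum-adjusted test stayed at about 5%.

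**4. How much of the gain stratification already delivers.** In the same simulations at a true difference of 6, power was 91.5% unadjusted against 92.9% adjusted at a stratum R² of 0.10, and 92.6% against 95.2% at 0.20. If the explained variance lies in the strata, adjustment therefore adds about 1 to 3 points. The whole gain in the table over 89.8% applies when the variance is explained by baseline LDL-C, which randomisation does not balance.

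**5. The choice between two tests.** Suppose the smaller of the two p-values were always taken. With 99 per arm and no stratum effect, simulated type I error is about 6.2% for normal data and up to about 7.1% for skewed or heavy-tailed data. With normal data and 20 balanced strata it is about 4.6 to 5.2% at a stratum R² of 0.10 and 3.4 to 3.8% at 0.20 (range over separate simulation runs). The conservatism in step 3 offsets the inflation.

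At the design difference of 6, with normal data, the two tests disagree on significance in about 3.6% of trials.

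**The case against.** The strongest reply is that nothing here is broken. The t-test matches the hypothesis and the sample-size formula, the planned power does not rely on covariates, and the only error from ignoring the strata runs against the sponsor. This stands. A reader might infer that the primary test is invalid or the trial underpowered, and the figures contradict both.

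The gain also rests on an R² that the protocol does not supply. Percent change already removes part of the dependence on baseline, and at R² = 0 there is no gain. That stands too, so zero is included in the range.

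A reader might also infer that leaving two tests open raises the type I error to 6–7%. That needs two conditions: deliberate selection of the smaller p-value, which the protocol nowhere describes, and strata that explain little. The pairing recurs for most continuous endpoints and reads as shorthand for a parametric or a rank test according to the distribution. The rule for choosing is a detail that a statistical analysis plan could hold, so its absence is not the finding.

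Finally, the target-attainment analysis might seem to need a combined stratified test. But the objective itself is attainment within each risk group: "The percentage of subjects achieving the target LDL-C by risk group at Week 12 after administration will be set as follows and compared" between the treatment groups, with a different target for each. A Cochran–Mantel–Haenszel test would answer a different question. It is optional and not part of this point.

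The reply does not meet the positive statement in the text. The protocol names unadjusted tests for a stratified trial and offers, as an alternative, a test that does not match its own hypothesis.

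**Conclusion.** The point holds as a free improvement, rated should-fix. The protocol's primary test is valid and its sample size and power stand, but the test leaves out information that the design itself uses.

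The size depends on an assumed R². Against 89.8% unadjusted, power at 99 per arm would be 91.2, 92.6 or 95.1% for R² of 0.05, 0.10 or 0.20, and the confidence interval would narrow by 0.1 to 0.4 percentage points on each side. The power gain is smaller, about 1 to 3 points at an R² of 0.10 to 0.20, where the strata alone explain the variance, and nil at R² = 0. If the strata explain 10–20%, the nominal 5% test runs at about 3.9–2.8%.

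The 6–7% type I error is a worst case under free selection with uninformative strata. It should not be read as the expected error of the plan. Confidence is high on what the text says and on the direction of the effect if the covariates predict response. The size of the effect is uncertain.

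**What to change.** In Protocol 11.2.3 and the synopsis, replace the paired options by one primary analysis: an ANCOVA of percent change in LDL-C at Week 12 on treatment, baseline LDL-C (continuous), risk group and site. Report the adjusted mean difference with its 95% CI. State beforehand how small sites are handled, by pooling or by a random site effect, because the number of sites is not given in the text at hand. Keep a rank test, preferably stratified, as a sensitivity analysis only. Use the same model with the matching baseline value for the continuous secondary endpoints: the other lipids, HbA1c and glucose.

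The cost is wording in the protocol, carried into the statistical analysis plan before data are seen. Risk group, site and baseline values are already collected. The 248 subjects need not change, and the sample-size calculation in 11.4 can stay, as it makes no allowance for any covariate gain.

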#### 11.2.4 Statistical Analysis of Exploratory Data

By calculating an ACER using the formula below, how much cost is added or saved per unit of an improved effect of the study group compared to the control group will be explored.

$$ACER = \frac{mean(C_T - C_N)}{mean(E_T - E_N)}$$

$\Delta C$ : difference in the average cost between the study group and the control group,

$\Delta E$ : difference in the average effect on LDL-C between the study group and the control group

#### 11.2.5 Statistical Analysis of Safety Data

The safety endpoints will be analyzed on the safety analysis set.

- 1) Adverse event (AE)
 

AEs will be coded using MedDRA version 20.0. The number of subjects and incidence (%) will be presented by SOC, and the chi-square test or the Fisher's exact test will be performed for comparison between the groups. The AEs that occur in the subjects will be classified into ADRs, SAEs, and SADR and analyzed in the same way.

In addition, for unexpected AEs that are not reflected in the labeled information, the number of subjects and incidence (%) will be presented by SOC and Preferred Terms (PT), and the chi-square test or the Fisher's exact test will be performed for comparison between the groups. As with the analysis of the AEs, unexpected AEs will be classified into ADRs, SAEs, and SADR and analyzed in the same way.
- 2) Vital signs
 

For vital signs results, descriptive statistics will be presented by time point, and change will be compared between the treatment groups using the independent samples t-test or the Wilcoxon rank sum test. The comparison within the treatment group will be performed using the paired samples t-test or Wilcoxon signed rank test.
- 3) Laboratory tests
 

The number and percentage (%) of subjects determined to be clinically significant abnormal based on laboratory test results will be presented by treatment group, and comparison between before and after administration will be performed using the McNemar test, and comparison between the treatment groups will be performed using the chi-square test or the Fisher's exact test.

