### 5.3 Exclusion Criteria

1. Uncontrolled following diseases
  - Diabetes mellitus (HbA1c  $> 9\%$  at screening)
  - Hypertension (systolic blood pressure  $\geq 180$  mmHg or diastolic blood pressure  $\geq 110$  mmHg at screening)
  - Thyroid dysfunction (TSH  $\geq 1.5$  x upper limit of normal [ULN] at screening)
2. Severe renal or hepatic impairment, active liver diseases, or serum creatinine, AST, or ALT  $\geq 2$  x ULN
3. Myopathy such as musculoskeletal disorders or rhabdomyolysis, or CPK (CK) level  $\geq 2$  x ULN
4. Medical or surgical conditions that may affect absorption, distribution, metabolism, and excretion of the investigational product (IP)
  - History of major gastrointestinal surgeries including gastrectomy, gastrointestinal bypass graft, and gastrointestinal anastomosis (excluding simple appendectomy and hernia repair)
  - History of active inflammatory bowel syndrome within the last 12 months
  - Pancreatic dysfunction (e.g., cholestasis) such as Crohn's disease and pancreatitis currently requiring treatment, or gastrointestinal/rectal bleeding
5. History of hypersensitivity or allergies to any ingredient of the IP
6. History of drug or alcohol abuse within the last 6 months
7. Patients who do not agree to use contraception (Women who have been amenorrheic for at least 12 months will be considered to be postmenopausal)
8. Patients who took other investigational agent within 30 days prior to the first dose of the IP
9. Patients who are difficult to stop drugs that affect the lipid levels after informed consent or require administration of other hypercholesterolemia drugs during the study
10. Patients who require administration of any prohibited concomitant medication specified in this protocol during participation in the study
11. Hereditary disorders such as galactose intolerance, Lapp lactase deficiency, or glucose-galactose malabsorption because this drug contains lactose
12. Inability to participate in the study by law or at the judgment of the investigator

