### 8.3 Packaging

The IPs will be manufactured and packaged by Chong Kun Dang Pharmaceutical Corp. and supplied to the study pharmacists at the study sites in accordance with the 'Regulation on the Safety of Pharmaceuticals, etc.' This study will be an open-label study. The IPs provided during the study will be packaged in a tight container and provided in an open-label manner.

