### **10.3.3 Laboratory tests**

Percentage of clinically significant abnormal laboratory results

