#### 10.4.3 Assessment of Severity

Severity of AEs will be determined by the principal investigator or the study staff based on their clinical judgment. It will be based on the maximal intensity and can be classified by the criteria below.

| Grade | Description                                                                                                          |
|-------|----------------------------------------------------------------------------------------------------------------------|
| 1     | Mild
No special treatment required.
Abnormal laboratory test or radiography results, etc. without any symptoms |
| 2     | Moderate
Simple, local, or non-invasive treatment, etc.                                                           |
| 3     | Severe
Hospitalization or invasive treatment such as transfusion, therapeutic endoscopy, or surgery required      |

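### Laboratory safety rests on an undefined clinically significant label in an open-label trial, and the protocol plans no analysis of the AST, ALT, CPK or creatinine values, so a moderate dose effect on them can pass unseen

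*Protocol*

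**What the plan says.** Section 10.3.3 defines the laboratory safety endpoint in one line: "Percentage of clinically significant abnormal laboratory results". Section 11.2.5(3) analyses it in three ways:

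- Summary: "The number and percentage (%) of subjects determined to be clinically significant abnormal based on laboratory test results will be presented by treatment group".
- Within arm: "comparison between before and after administration will be performed using the McNemar test".
- Between arms: "comparison between the treatment groups will be performed using the chi-square test or the Fisher's exact test".

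Neither section states what makes a result clinically significant or names an assessor. Section 8.3 says "This study will be an open-label study". Laboratory tests are run fasting at a central laboratory, and Visit 4 (Week 12) is the only scheduled on-treatment sample (Summary of Study Schedule, section 10.1).

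Other measurements are treated differently. For vital signs, section 11.2.5(2) says "For vital signs results, descriptive statistics will be presented by time point, and change will be compared between the treatment groups", and section 11.2.3 compares HbA1c and glucose as mean change. The protocol does use numeric limits at entry: section 5.3 excludes subjects with "Severe renal or hepatic impairment, active liver diseases, or serum creatinine, AST, or ALT" at or above 2 x ULN, and applies the same multiple to CPK.

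**The concern.** Comparing the safety of two doses of one statin is a stated secondary objective (section 4), and section 3.1 says the sponsor hopes to show no significant difference in adverse event incidence. For that purpose the laboratory endpoint has two weaknesses.

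First, it is a yes/no label without a rule. Two sites can label the same value differently, and nothing in the protocol keeps the person deciding from knowing the dose.

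Second, reducing a measured value to a rare yes/no event discards most of its information. With about 124 subjects per arm and events in a few percent, the between-arm test will rarely reject. A non-significant result could then be read as reassurance although the analysis could hardly have shown anything else. The numeric values that could answer the question are collected but not used.

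**Working it through.** **Arm sizes.** The protocol states no figure for laboratory safety, so the sample size in section 11.4 supplies only n. It reproduces: 2 x (1.96 + 1.28)² x 13² / 6² = 98.56, so 99 per arm; 99 / 0.8 = 123.75, so 124 per arm and 248 in total. The safety set (section 11.1.3) is every randomised subject who took a dose, so 124 per arm is the upper figure. About 99 applies if 20% have no Week 12 sample.

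**Power of the planned between-arm test.** All event rates are assumptions. Power is the sum of Bin(x; n, p1) x Bin(y; n, p2) over all pairs (x, y) for which the two-sided Fisher p is at most 0.05. The normal approximation, closer to the chi-square option, is in brackets.

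| Assumed rates | 124 per arm | 99 per arm |
|---|---|---|
| 1% vs 2% | 1% (10%) | 1% (8%) |
| 1% vs 3% | 6% (20%) | 3% (17%) |
| 1% vs 5% | 29% (45%) | 19% (38%) |
| 2% vs 6% | 23% (36%) | 17% (30%) |
| 3% vs 10% | 51% (61%) | 42% (52%) |

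If one arm has no cases, the other needs at least 6 for Fisher significance (p = 0.029 at either size).

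**Power of a numeric comparison.** With standardised difference d, power is about Φ(d x √(n/2) − 1.96). At n = 124, √62 = 7.874:

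- d = 0.3: Φ(2.362 − 1.96) = Φ(0.402) = 66%
- d = 0.4: Φ(3.150 − 1.96) = Φ(1.190) = 88%
- d = 0.5: Φ(3.937 − 1.96) = Φ(1.977) = 98%

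At n = 99 the figures are 56%, 80% and 94%.

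**One model for both.** The two sets above assume different kinds of effect, so a simulation put them on a common footing. Assumptions: log-normal ALT with median 0.55 x ULN, between-subject log SD 0.40, within-subject log SD 0.25, baseline cut at 2 x ULN, 124 per arm, and shifts of +5% and +20% in the two arms. The change-from-baseline t-test rejected in about 85% of runs. As a check, log(1.20/1.05) = 0.1335; the SD of change is 0.25 x √2 = 0.354; d = 0.378; Φ(0.378 x 7.874 − 1.96) = Φ(1.01) = 84%. Fisher on values at or above 1 x ULN rejected in about 25% of runs. At 2 x ULN it rejected in about 0%, because only about 0.3% and 0.8% of subjects reached that level.

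**The within-arm McNemar test.** If clinically significant means roughly 2 x ULN or more, the baseline count for the four analytes is zero by exclusion, so discordant pairs can run only towards abnormal afterwards. Six against none gives exact two-sided p = 2 x 0.5⁶ = 0.031; five gives 0.0625. With no drug effect the simulation had 0% at baseline and about 0.2% at Week 12.

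**The case against.** **A second route exists.** The adverse event definition in section 10.4.1 includes abnormal laboratory results, and adverse events are compared between arms by System Organ Class and again as drug reactions and serious events. This stands: it would be wrong to say laboratory signals are read only through the clinically significant label. The route is coarse, though. Preferred Terms are planned only for unexpected events, so a labelled ALT or CPK rise is pooled within its class, and capture depends on site reporting.

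**The analysis plan may add more.** ULN categories, shift tables and numeric summaries are often left to a statistical analysis plan, which is not shown, and the protocol does not forbid them. Their absence alone is therefore no finding. What remains is that sections 10.3.3 and 11.2.5(3) themselves fix the endpoint and tests on an undefined label.

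**Unblinded judgement is an inference.** No assessor is named and the values come from a central laboratory. The open-label design permits a call made knowing the dose; the protocol does not say this will happen.

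Two stronger readings are tempting:

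- A reader might infer that the entry limits help to hide a dose effect. They do not. They act before randomisation, equally in both arms, and push the McNemar test towards showing a rise. The push is also small: at a 0.2% no-effect rate, six or more cases among 124 has a chance of about 2 in 10 million, and at 1% about 0.2%.
- A reader might infer that the severity scale in section 10.4.3, where Grade 1 takes in "Abnormal laboratory test or radiography results, etc. without any symptoms", masks large symptom-free rises. No analysis planned in section 11.2.5 uses severity grade, so it cannot conceal a difference in any planned comparison.

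**Conclusion.** The point holds for the between-arm laboratory comparison. The protocol's only laboratory safety endpoint has no criterion and no named assessor in an open-label trial, and the protocol plans no numeric analysis of AST, ALT, CPK or creatinine. A moderate dose effect on these values can therefore pass unseen: about 1% to 29% Fisher power at 124 per arm for assumed rates of 1% versus 2% up to 1% versus 5%, against about 66% to 98% for a numeric comparison at assumed standardised differences of 0.3 to 0.5.

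These figures rest on assumed rates, effect sizes and ALT spread, since the protocol gives none. They show how insensitive the planned test is; they do not predict a dose effect. A shift in the mean is also not the same as a clinically important rise, so the numeric analysis should sit beside categories that catch rare large values. The efficacy conclusions and the sample size are unaffected. The change is worth making but not critical.

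**What to change.** In section 11.2.5(3), with matching wording in 10.3.3:

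1. For AST, ALT, CPK and creatinine, add descriptive statistics by arm and a between-arm comparison of change from baseline to Week 12 with a confidence interval. This should lead. A proportion at or above 2 x ULN would be objective, but on its own too insensitive.
2. Add categories by multiple of ULN and baseline-to-Week-12 shift tables by arm.
3. Keep the clinically significant call as supportive, and state its criterion and who applies it.
4. For the four analytes with an entry limit, show before/after counts descriptively in place of the McNemar p-value, because exclusion at 2 x ULN lets that test move mainly towards a rise. This does not affect the between-arm comparison.

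The cost is a few sentences and a few extra tables from central-laboratory data already collected, with no new visits or samples. The drawback is that fixed categories will count some rises an investigator would call unimportant.
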